## Abstract

**Highlights:**

**Public health relevance—How does this work relate to a public health issue?**
This protocol is motivated by the high burden of workplace accidents and musculoskeletal disorders among food-supply chain workers, a sector of major importance for public health and economic stability in Italy.It targets conditions that are among the leading global causes of disability, long-term functional impairment, and healthcare utilization.

**Public health significance—Why is this work of significance to public health?**
It applies a multidimensional “One Health” approach that integrates nutritional, psychological, biochemical, and body-composition indicators domains that are rarely assessed together in real-world occupational settings.The generation of harmonized and reproducible data will support system-level prevention strategies aimed at reducing avoidable disability, sick leave, and downstream healthcare costs in the food supply chain sector.

**Public health implications—What are the key implications or messages for practitioners, policy makers and/or researchers in public health?**
The protocol provides an operational framework for the early identification of high-risk worker subgroups, informing targeted nutritional and psychosocial preventive interventions.Its multidisciplinary design can assist policymakers and occupational health services in developing integrated surveillance and prevention systems tailored to the food-supply chain, strengthening workforce resilience and public health preparedness.

**Abstract:**

The agri-food supply chain is a relevant contributor to the Italian economy but shows a high incidence of occupational injuries and musculoskeletal disorders, such as lower back pain. Repetitive manual handling and biomechanical overload highlight the need for a prevention-oriented, system-level assessment. This protocol aims to implement a harmonized One Health approach procedure for the multidimensional evaluation of food supply chain workers in real-world settings. The protocol integrates bioelectrical impedance vector analysis (BIVA), nutritional parameters, quality-of-life and psychological measures, and assessments of systemic oxidative stress and systemic serotonin levels. Data from active workers will be compared with those from sedentary individuals. The study will evaluate whether BIVA profiles differ between these groups and examine how the additional indicators contribute to a multidimensional well-being framework. By operationalizing an integrated One Health approach that bridges nutritional, psychological, and biomarker domains, this protocol is designed to guide targeted preventive and educational strategies and inform evidence-based occupational and public health policies across the food supply chain. Trial registration: NCT06896877 (ClinicalTrials.gov), 26 March 2025.

## 1. Introduction

### 1.1. Background

The agri-food supply chain employs a large workforce across primary production, processing, distribution and food services, and represents a structurally relevant domain in terms of value added and employment in Italy [1]. Over the last ten years, the food industry has grown by more than 10%, with a steady and significant increase in the share of exports based on the importance of the “Made in Italy” label.

Despite the operational resilience also documented during emergency scenarios such as COVID-19, this sector remains among those with the highest incidence of occupational injuries and work-related diseases, particularly musculoskeletal disorders [2]. Repetitive manual handling, sustained awkward postures and biomechanical overload persist despite technological advances, and contribute to the upstream burden of conditions such as low back pain, which is the leading cause of disability worldwide [3,4,5]. Consequently, preventive action against these exposures may help reduce the likelihood and severity of disorders, and in turn may contribute to limiting downstream consequences such as prolonged sick leave, hospitalization or the need for rehabilitation.

Given the strategic relevance of the food supply chain in the Italian context, an integrated approach to ensuring the comprehensive protection of workers in this sector is essential. For this reason, the One Health Framework was deliberately adopted as the conceptual foundation of the present study. Defined as a multidimensional model shaped by interdependent human, environmental, and systemic determinants, the One Health Framework aligns with the WHO definition of health as “a state of complete physical, mental and social well-being and not merely the absence of disease or infirmity” [6,7].

Understood as an intrinsically multidimensional model that links human, environmental, and systemic determinants of health, the One Health Framework guides the design, data collection strategy, and analytical plan of this protocol. Its adoption enables a prevention-oriented perspective, as upstream determinants affecting workers’ physical, nutritional, psychological, and biochemical status have implications not only for individual well-being but also for workforce functionality, production stability, and downstream public health.

Despite existing research on ergonomics and mental health in occupational settings, there is a lack of integrated protocols that simultaneously combine nutritional indicators, psychological assessments, and biomarkers within a unified prevention-oriented approach. This study addresses this gap by operationalizing a comprehensive One Health approach that bridges these domains, providing a holistic understanding of worker health that can inform both occupational and public health policy.

Current evidence on agri-food workers remains largely domain-specific: studies typically focus separately on mental health, heat-related risks, or ergonomic exposures, and reviews document fragmented findings by domain [8,9], while no integrated assessments combine nutritional, compositional, psychological and biological dimensions within a unified prevention-oriented framework. Determinants such as nutritional status, body composition, hydration, and emotional well-being influence musculoskeletal resilience and overall health [10,11,12,13].

Beyond nutritional status, quality of life and emotional–affective functioning are fundamental components of worker well-being. Approximately 15% of working-age adults experience a mental disorder during their lifetime [14] and the COVID-19 pandemic produced an estimated 25% increase in anxiety and depression in 2020 [15,16]. Mental health disorders contribute to sick leave and productivity loss, with repercussions for organizational sustainability [17,18]. In recognition of this burden, recent WHO guidelines emphasize the systematic assessment of psychosocial risks and mental health in the workplace through validated instruments on mood, stress, satisfaction and organizational climate [14,19].

In parallel to psychological and behavioural indicators, selected biological markers have been investigated as correlates of altered well-being. Serotonin (5-HT), a tryptophan-derived monoamine regulating circadian rhythms and satiety, has been implicated in mood, anxiety, sleep and cognition. Reduced serotonergic tone has been linked to depressive-related cognitive impairments, including reduced flexibility, memory and attentional control [20,21], and low extracellular 5-HT may compromise memory consolidation [22]. The systemic oxidative state—reflecting the balance between pro-oxidant and antioxidant species—has been associated with inflammatory, respiratory, metabolic, cardiovascular, oncologic, neurodegenerative and anxiety conditions [23,24,25,26].

Body composition is a relevant intermediate indicator linking nutritional and functional status to musculoskeletal risk. Bioimpedance-based assessment provides a non-invasive measure capable of capturing hydration and cellular integrity, which are associated with functional capacity and vulnerability to biomechanical load. Despite its applicability in occupational settings, such measures have not been integrated with psychological, nutritional and biochemical indicators in agri-food workers.

This observational exploratory study aims to generate an integrated assessment of food supply chain workers by combining indicators of nutritional status, bioimpedance-based body composition, psychological well-being, quality of life, and biomarkers of oxidative stress and serotonin. This multidimensional data collection is expected to identify critical issues and modifiable targets, supporting the design of sector-specific preventive and educational strategies.

### 1.2. Aim and Hypothesis

This exploratory observational study primarily aims to assess whether differences in nutritional status and body composition—as indexed by bioimpedance-based assessment of body cell mass and hydration—exist between sedentary and physically active workers in the food supply chain.

As secondary exploratory aims, we will: (i) assess quality of life and emotional–affective well-being using validated instruments, in order to identify psychological or social critical issues related to work in the food supply chain; (ii) characterize nutritional status and dietary habits to detect potential deficiencies or excesses; (iii) quantify systemic biomarkers of oxidative stress and circulating serotonin levels; (iv) identify risk classes, i.e., subgroups of workers at potentially higher disease risk due to inadequate dietary patterns and/or exposure to occupational stressors; (v) assess sex-related differences in nutritional status, oxidative stress biomarkers, and psychological outcomes, to inform the potential need for gender-specific preventive or dietary recommendations; and (vi) analyze the standardized phase angle (SPhA) as an integrative marker of cellular health and systemic status, and explore its potential associations with nutritional, biochemical and psychological indicators on an exploratory basis.

## 2. Experimental Design

### 2.1. Study Design

This study protocol describes a monocentric, observational, non-profit investigation conducted on workers employed in the food supply chain. A total of 40 participants will be recruited from workers directly or indirectly connected with the Experimental Centre “Centro Santa Maria della Provvidenza”, of the Don Carlo Gnocchi Foundation in Rome, Italy. Information about the study will be disseminated to workers through internal communications, corporate informational materials and dedicated dissemination meetings. Participation will be requested by the investigator on a voluntary basis.

Anamnestic data will be collected using Case Report Forms (CRFs). Nutritional status, oxidative stress and serotonin levels will be assessed, and quality of life and emotional–affective status will be evaluated using validated questionnaires. Moreover, surveys covering general, nutritional, psychological and occupational health domains will be administered in subsequent study phases for exploratory purposes. An informational brochure promoting healthy dietary practices will be delivered to all participants during the evaluation phase.

Figure 1 shows the study flow chart, in compliance with the Centralised Protocol Items Recommendations for Observational Studies (SPIROS) guidelines (see Table S1).

The total duration of the study will be six months, with completion expected by 30 November 2025. During this period, specific days will be scheduled to convene participants, during which all assessments planned in the protocol will be conducted in a single session (T0). At this time, participants will be provided with the link to access and complete the online surveys. The study protocol is registered at ClinicalTrials.gov ID: NCT06896877. The study protocol is registered at ClinicalTrials.gov under the name “Nutrition status and emotional well-being of the worker-consumer in the food supply chain. (ONEHEALTH)” on 26 March 2025 and ID: NCT06896877.

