#### 3.2.3. Eating Habits Questionnaire

The participant will also complete a survey on dietary habits, including daily water intake and consumption of other beverages (including alcoholic drinks), adherence to the Mediterranean diet (weekly intake of olive oil, nuts, cereals and whole grains, vegetables, meat, dairy products, processed and industrial foods, chocolate, coffee and tea), as well as the presence of specific dietary regimens and eating habits.

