#### 3.2.4. Healthy Eating Education

To promote healthy dietary practices, during the evaluation, we will deliver an informational brochure providing guidance for a healthy lifestyle, based on the principles of the Mediterranean diet and in accordance with the criteria outlined by the National Recommended Energy and Nutrient Intake Levels for the Italian Population [35]. In the brochure, there is a link to the dietary Guidelines from CREA-AN [36]. These guidelines are part of a multifaceted solution to encourage health and prevent diet-related chronic diseases, including cardiovascular disease, type 2 diabetes, some cancers, and obesity. It is a consensus document accepted and endorsed by the scientific community and civil society stakeholders [37].

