Standardized phase angle (SPhA), adjusted to sex- and age-specific references, will be analyzed as a continuous endpoint. The primary comparison (active vs. sedentary) will use a two-sample t-test. A sensitivity ANCOVA adjusting for BMI (and other prespecified covariates, if applicable) will assess robustness. The proportion of participants with SPhA ≤−1.65 (≈5th percentile) will be compared between groups using χ^2^ or Fisher’s exact test (reporting risk ratio and 95% CI). Secondary exploratory outcomes, deriving from nutritional, biochemical, and psychological domains’ assessment, will be analyzed with χ^2^/Fisher for categorical variables and t-test/Mann–Whitney for continuous variables depending on normality (assessed with Shapiro–Wilk). Effect sizes with 95% confidence intervals will be reported. Age will be included as a continuous covariate in sensitivity MAN(C)OVA and ANCOVA models. Exploratory analyses will also examine age-related associations with bioimpedance, psychological, and biomarker measures.

Exploratory associations among nutritional indicators (SPhA), bioimpedance parameters, oxidative-stress markers, serotonin, and psychological measures will be examined using Pearson or Spearman coefficients as appropriate. No directional hypotheses are pre-specified for these exploratory analyses; findings will be interpreted as hypothesis-generating.

No missing data are expected because all measurements will be collected during supervised in-person sessions. Data completeness will be verified at the time of assessment. If unexpected missingness occurs, analyses will follow a complete-case approach and the extent of missing data will be reported.

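### The diet brochure is handed out during the evaluation while surveys with a nutritional domain follow online, which risks prompted dietary answers and undercuts the reason given for expecting no missing data

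*Protocol article*

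**What the plan says.** **Brochure.** Section 2.1 says: "An informational brochure promoting healthy dietary practices will be delivered to all participants during the evaluation phase". Section 3.2.4 repeats the timing and gives the content: "during the evaluation, we will deliver an informational brochure providing guidance for a healthy lifestyle, based on the principles of the Mediterranean diet".

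**Surveys.** Section 2.1 says that "surveys covering general, nutritional, psychological and occupational health domains will be administered in subsequent study phases for exploratory purposes". It then says that "all assessments planned in the protocol will be conducted in a single session (T0", and continues: "At this time, participants will be provided with the link to access and complete the online surveys". Neither the place nor a deadline for completing them is given.

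**Dietary-habits instrument.** Section 3.2.3 says: "The participant will also complete a survey on dietary habits, including daily water intake and consumption of other beverages". It goes on to cover adherence to the Mediterranean diet food group by food group. Neither the time nor the mode of completion is stated.

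**Missing data.** Section 3.6 says: "No missing data are expected because all measurements will be collected during supervised in-person sessions". Should data be missing after all, it provides for complete-case analysis and for reporting how much is missing.

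**What the dietary data serve.** Under Section 1.2, secondary aim (ii) covers nutritional status and dietary habits, with a view to finding deficiencies or excesses. Aim (iv) forms risk classes that draw partly on inadequate dietary patterns.

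**The concern.** There are two separate problems, and they meet in the same surveys.

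The first is order. A participant who has just been given guidance on a healthy diet, and is then asked what he or she eats, has been shown the favoured answers. Replies may move toward the recommendation, or habits may change before a later survey is filled in. Aims (ii) and (iv) use absolute levels: how many workers fall short, and who belongs in a risk class. A shift common to all participants does not cancel out of such quantities; it makes inadequacy look rarer than it is. Once the brochure has been read, unprompted answers cannot be recovered.

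The second is the missing-data premise. The reason given for expecting complete data is supervised, face-to-face collection. A survey reached through a link and placed in a later phase is not collected that way on its face, so the premise fails for exactly the instruments most open to non-response.

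**Working it through.** **1. Order of events, setting the statements side by side.**

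| Item | Where stated | Timing as written |
|---|---|---|
| Brochure | 2.1 and 3.2.4 | during the evaluation |
| Surveys with a nutritional domain | 2.1 | later phases; online; link given at T0 |
| All planned assessments | 2.1 | one T0 visit |
| Dietary-habits survey | 3.2.3 | not stated |

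The first two rows put the nutritional survey answers after the brochure. The third row contradicts the second. The fourth leaves open whether the dietary-habits survey is one of the online surveys or a form completed at the visit. Nothing in the article says that dietary questions are finished before the brochure is given.

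**2. Overlap of content.** The brochure rests on Mediterranean-diet principles (3.2.4), and the dietary-habits survey asks about adherence to that diet (3.2.3). If that survey is among those completed later, the education and the measurement concern the same behaviour.

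**3. Which results are exposed.**
- Absolute levels of reported diet, and risk classes built on them: exposed.
- Active-versus-sedentary difference in reported diet: everyone gets the same brochure. If reporting shifts by s_A in active and s_S in sedentary workers, the difference is biased by s_A − s_S, which is zero when the groups react alike.
- R/H and Xc/H, anthropometry and fasting blood at T0: a brochure given that day would not plausibly change them.

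**4. Missing-data premise.** Section 3.6 claims supervision for all measurements; Section 2.1 describes online surveys through a link and in later phases. The two cannot both hold for those surveys unless they are completed on site, which the article does not say.

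**5. Loss of precision under non-response (illustration).** The plan gives no figure on this point to reproduce. Inputs: about 20 per group (Section 3.6); response rates of 60% to 100%, which are an assumption, taken as equal in both groups.

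Half-width of the 95% interval for a group difference, in SD units, with n per group: t(0.975, 2n − 2) × √(2/n).

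| Response | n per group | Total | Half-width (SD) |
|---|---|---|---|
| 100% | 20 | 40 | 0.64 |
| 90% | 18 | 36 | 0.68 |
| 80% | 16 | 32 | 0.72 |
| 70% | 14 | 28 | 0.78 |
| 60% | 12 | 24 | 0.85 |

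For example, 2.02 × √(2/20) = 0.64 and 2.07 × √(2/12) = 0.85. At 60% response the interval is 0.85/0.64 = 1.33 times as wide. These figures measure lost precision only. They say nothing about the size of a reporting shift or of selection.

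**The case against.** The strongest reply is that the order is not actually fixed. The brochure is tied only to the evaluation, all planned assessments are said to take place in one visit, and the link is handed over at that visit, so completion on the spot before the brochure is a possible reading. The dietary-habits survey stands in Section 3.2 beside anthropometry and bioimpedance, and Section 2.3 says data are first collected on paper forms. It may therefore be a separate T0 instrument, with the online surveys an addition. Aim (ii) also rests on anthropometry, bioimpedance and blood indices. The affected outcomes are exploratory, Section 3.6 disclaims confirmatory power for them, and the complete-case rule with reporting of missingness is already there. For single-outcome tests, that rule amounts to using everyone who has the outcome. Session logistics are also often left to the full protocol, which is not shown.

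Much of this stands, and it limits the point to a risk. A reader might infer that the dietary data as a whole are contaminated; the article does not support that, because the timing of the Section 3.2.3 survey is not stated. A reader might also infer that non-responders would differ by job type or mood. That is conceivable, but nothing in the text bears on it.

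What does not fall away is that the only timing given for the nutritional-domain surveys puts them after the evaluation in which the brochure is delivered, that Section 2.1 contradicts itself on one visit versus later phases, and that the reason in Section 3.6 does not fit online collection. These are conflicts between printed statements, not details left out.

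**Conclusion.** The point holds as a risk to exploratory survey outcomes and as an inconsistency in the text. As written, nutritional survey answers follow the diet education and may move toward the recommended pattern, which would understate inadequacy in the dietary-habits part of aim (ii) and in the risk classes of aim (iv). The Section 3.2.3 survey shares this exposure only if it is one of the later online surveys. The size of any shift cannot be derived from the document.

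The reason for expecting no missing data is not valid for the online surveys. Under an assumed response of 60% to 90%, equal in both groups, the half-width of a group difference would be 0.68 to 0.85 SD instead of 0.64 SD.

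The primary bioimpedance comparison and the T0 blood measures are untouched, and the contrast between active and sedentary workers is biased only if the two groups respond differently to the brochure. The change is worth making because it is almost free and removes an avoidable bias that the analysis cannot correct afterwards.

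**What to change.** 1. Have participants complete the dietary and all other surveys on site at T0, using the link on a tablet or their own phone, and hand over the brochure only after submission.
2. State in Section 3.2.3 when and how the dietary-habits survey is completed, and whether it is one of the online surveys.
3. Reconcile the two statements in Section 2.1, one placing all assessments in a single visit and the other placing surveys in later phases.
4. In Section 3.6, confine the expectation of complete data to measurements taken in person, state that each analysis uses all participants with that outcome, and report survey response by group.

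The cost is a re-ordered session and a few more minutes per participant. No additional data or staff are needed.
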